## Abstract

**Background:**

Bipolar disorder (BD) is a highly prevalent psychiatric condition that can significantly impact every aspect of a person’s life if left untreated. A subtype of BD, bipolar disorder type II (BD-II), is characterized by long depressive episodes and residual depression symptoms, with short-lived hypomanic episodes. Medication and psychotherapy, such as cognitive behavioral therapy (CBT), are the main treatment options for BD-II. CBT specific for BD-II involves the recognition of warning signs, potentially triggering stimuli, and the development of coping skills to increase euthymic periods and improve global functioning. However, access to in-person CBT may be limited by several barriers, including low availability, high costs, and geographical limitations. Thus, web-based adaptations of CBT (e-CBT) have become a promising solution to address these treatment barriers. Nevertheless, e-CBT for the treatment of BD-II remains understudied.

**Objective:**

The proposed study aims to establish the first e-CBT program specific for the treatment of BD-II with residual depressive symptoms. The primary objective of this study will be to determine the effect of e-CBT in managing BD symptomatology. The secondary objective will be to assess the effects of this e-CBT program on quality of life and resilience. The tertiary objective will involve gathering user feedback using a posttreatment survey to support the continuous improvement and optimization of the proposed program.

**Methods:**

Adult participants (N=170) with a confirmed diagnosis of BD-II experiencing residual depressive symptoms will be randomly assigned to either the e-CBT and treatment as usual (TAU; n=85) group or the TAU (n=85) control group. Participants in the control group will be able to participate in the web-based program after the first 13 weeks. The e-CBT program will consist of 13 weekly web-based modules designed following a validated CBT framework. Participants will complete module-related homework and receive asynchronous personalized feedback from a therapist. TAU will consist of standard treatment services conducted outside of this research study. Depression and manic symptoms, quality of life, and resiliency will be assessed using clinically validated symptomatology questionnaires at baseline, week 6, and week 13.

**Results:**

The study received ethics approval in March 2020, and participant recruitment is expected to begin in February 2023 through targeted advertisements and physician referrals. Data collection and analysis are expected to conclude by December 2024. Linear and binomial regression (continuous and categorical outcomes, respectively) will be conducted along with qualitative interpretive methods.

**Conclusions:**

The findings will be the first on the effectiveness of delivering e-CBT for patients with BD-II with residual depressive symptoms. This approach can provide an innovative method to address barriers to in-person psychotherapy by increasing accessibility and decreasing costs.

**Trial Registration:**

ClinicalTrials.gov NCT04664257; https://clinicaltrials.gov/ct2/show/NCT04664257

**International Registered Report Identifier (IRRID):**

PRR1-10.2196/46157

## Introduction

Bipolar disorder (BD) is a highly prevalent affective psychiatric condition that affects nearly 2% of the global population [1-5]. It is characterized by chronic mood swings fluctuating from mania or hypomania to depression, which often cause significant impairment both socially and occupationally. The manic or hypomanic component involves 3 days or more of persistently elevated mood, recklessness, grandiosity, decreased need for sleep, reduced ability to concentrate, and irritability [2,4,6-8]. The depressive component involves 2 weeks or more of persistently low mood, anhedonia, poor appetite and sleep, reduced ability to concentrate, agitation or motor slowness, and suicidal ideation [4,8]. There are 4 main types of BD that are differentiated by the type, frequency, and severity of the mood episodes. Bipolar I disorder requires at least one manic episode, whereas bipolar disorder type II (BD-II) is characterized by depressive and hypomanic episodes. Cyclothymic disorder involves the presence of depressive and hypomanic states that do not meet diagnostic criteria and last a minimum of 2 years. Lastly, BD with mixed features is characterized by depressive and elevated moods simultaneously [2,4]. Unlike other types of BD, individuals with BD-II tend to experience longer and more persistent depressive episodes, sometimes with residual depressive symptoms, which are further exacerbated by the negative consequences of their hypomanic episodes [8].

Misdiagnosis and delayed treatment are common for individuals with BD, which can result in serious and sometimes irreversible outcomes. These outcomes can include more frequent and severe mood episodes, intellectual disability, loss of independence, and loss of ability to function [2,4,6,7,9-12]. Although mood-stabilizing medication remains the first line of treatment for BD, the beneficial effects of psychosocial treatments, particularly cognitive behavioral therapy (CBT), are now widely recognized [13]. Furthermore, the use of psychotherapy for the management of BD-II has evolved significantly over the past few decades [8]. CBT targets negative or dysfunctional thought patterns and behaviors through cognitive and behavioral restructuring techniques. These techniques aim to help the individual develop healthier or more balanced thought patterns (cognitive restructuration), which can then be applied in day-to-day life (behavioral restructuration). This can help with reducing psychiatric symptomatology and decreasing depressive episode duration along with increasing euthymic periods and improving global functioning and quality of life [14-20]. Furthermore, CBT specific for BD-II often includes techniques to practice acceptance, recognize warning signs of an upcoming mood episode, recognize potentially triggering stimuli, and develop an action plan with helpful steps and considerations to follow before, during, and after a mood episode [8,14,16,17,19,21,22].

However, several barriers prevent the broader uptake of CBT and other in-person psychotherapy options, including high costs, low availability, long waitlists, stigma against psychiatric interventions, and geographical and physical limitations [11]. Thus, web-based adaptations of traditional in-person CBT (e-CBT) have become promising alternatives due to their lowered cost, time effectiveness, flexibility, privacy, and convenience [14,23-25]. Additionally, e-CBT has been shown to increase help-seeking behaviors among patients and to have similar effectiveness at reducing psychiatric symptomatology as in-person CBT [11,14,26-28]. e-CBT programs often include weekly assignments for the participants and may be either fully self-guided or guided with asynchronous support from an assigned therapist [14]. Despite these benefits over in-person CBT, e-CBT options specific to BD remain significantly understudied and underdeveloped, and very few e-CBT programs have focused on BD-II [15-19,29].

To supplement this gap in the literature and guide clinical practice, this will be an open-label randomized controlled trial studying the effectiveness of a novel e-CBT program specific for BD-II in addition to treatment as usual (TAU; e-CBT + TAU). This program will be developed with the help of individuals with lived experience of BD-II to ensure applicability and accuracy. Thus, the primary objective of this study will be to determine the changes in BD symptomatology (hypomanic and depressive symptoms) of participants receiving e-CBT + TAU compared to participants receiving only TAU. Based on the evidence comparing e-CBT specific for BD to psychoeducation, attention controls, and TAU [16,17,19], this study hypothesizes that adding this e-CBT program to TAU will result in better symptom management than TAU by itself. The secondary objective will be to assess the effects of this e-CBT program on quality of life and resilience. The tertiary objective will involve gathering user feedback using a posttreatment survey to support the continuous improvement and optimization of the proposed program.

## Methods

### Participants

This is the protocol for a randomized controlled trial studying the efficacy of a novel e-CBT program. Participants (N=170) diagnosed with BD-II experiencing residual depressive symptoms will be recruited from the Mood and Anxiety Clinic at Providence Care Hospital, Kingston Health Sciences Center, family physicians, other health care professionals, and self-referrals within Ontario, Canada. Additionally, recruitment efforts will be carried out through flyers in social gathering areas (eg, coffee shops, college campuses), media advertisements, and expert end user referrals. After providing consent to participate in the study, the participants will complete a Mini International Neuropsychiatric Interview 7.0.2 (MINI) with a trained research assistant [30]. The MINI assesses 17 common psychiatric conditions following the diagnostic criteria of the Diagnostic and Statistical Manual of Mental Disorders, 5th edition (DSM-5) [30]. Inclusion criteria include being 18 years or older at the start of the study, a diagnosis of BD-II based on the MINI assessment, a Montgomery-Åsberg Depressive Rating Scale (MADRS) score of mild to moderate depression symptomatology (MADRS score 7-34), competence to consent and participate, ability to speak and read English, and consistent and reliable access to the internet [14,31-33]. Exclusion criteria include acute hypomanic or manic episodes, acute psychosis, severe alcohol or substance use disorder, and active suicidal or homicidal ideation. Additionally, individuals who are currently receiving or have received CBT in the past 6 months will be ineligible to avoid confounding treatment effects.

### Procedures

Eligible participants will be randomly assigned to either a 13-week e-CBT program in addition to TAU (n=85; e-CBT + TAU group) or TAU only (control group; n=85). If interested, participants in the control group will be offered access to the e-CBT program after completing 13 weeks as part of the control group. The e-CBT program will be delivered as an augmentation to TAU through the Online Psychotherapy Tool (OPTT), a secure and interactive platform developed by the principal investigator (PI) [14,34]. TAU will consist of medications, regular physician or clinician visits, referrals, or consultations that are conducted outside of this research study.

### e-CBT Specific for BD-II

Participants in the e-CBT group will receive weekly predesigned web-based modules for 13 weeks. Each module will consist of approximately 30 slides and should take an estimated 45 minutes to complete. Each participant will be assigned a therapist to communicate with them asynchronously through the OPTT platform. In addition, the modules include weekly homework for the participants, which will be submitted directly through OPTT to the assigned therapists. The therapists will then use the OPTT platform to provide personalized feedback using session-specific therapy feedback templates. These feedback templates were developed under the guidance of the PI (NA) to standardize the quality and content of the feedback across different patients and therapists. Furthermore, in previous studies conducted by the PI, these feedback templates have been used to prepare personalized feedback in approximately 15-20 minutes [14,33,35,36].

The proposed e-CBT program will be developed to teach core CBT concepts (ie, the 5-part model, automatic thoughts, the thought record, cognitive and behavioral restructuration) and concepts specific to the management of BD-II [8,14,35,37]. These BD-II–specific concepts include techniques to practice acceptance, recognize warning signs of an upcoming mood episode, recognize potentially triggering stimuli, and develop an action plan with helpful steps and considerations to follow before, during, and after a mood episode [8,14,16,17,19,21]. Additionally, individuals with lived experience of BD-II will be recruited to help in module development and review the modules for applicability and accuracy.

### Training

Research assistants trained in the delivery of CBT and writing feedback will be assigned as therapists for the e-CBT group. The PI, who is an expert in the web-based delivery of psychotherapy and CBT [14,33,35-37], is involved in the training of the therapists to ensure the quality and reliability of the treatment programs. Training will involve weekly workshops and a CBT training video with a quiz at the end. To further ensure that the therapists are well prepared, the co-PI (MY) will closely guide the therapists through their first patient (assigning modules, reviewing homework, writing feedback, and answering questions using the OPTT platform). Furthermore, all therapists will use predesigned session-specific feedback templates to secure the quality of the feedback, which will be reviewed by the co-PI before being sent to the participants. To avoid a conflict of interest, the PI will not be involved in writing or supervising feedback.

### Outcome Evaluation

The primary outcome of this study will be to determine the change in BD symptomatology (hypomanic and depressive symptoms) of participants receiving e-CBT + TAU compared to participants receiving TAU only. This will be measured through clinically validated symptomatology questionnaires, including the MADRS and the Young Mania Rating Scale (YMRS) [31,32]. The secondary outcome will be to assess the effects of this e-CBT program on quality of life and resilience. These metrics will be assessed using the Quality-of-Life Enjoyment and Satisfaction Questionnaire-Short Form (Q-LES-Q-SF) [38] and the 14-item Resilience Scale (RS-14) [39]. All questionnaires will be completed through OPTT at baseline, week 6, and week 13. Subsequent to the treatment period, follow-up assessments will be conducted for all the outcome measures at 3, 6, and 12 months. The tertiary outcome will involve gathering user feedback using a posttreatment survey. This posttreatment survey will be sent to all participants who completed the e-CBT program and will consist of questions related to their experience going through the modules and using the OPTT platform. Also, it will collect any additional feedback and suggestions to support the continuous improvement and optimization of the proposed program.

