### Data Analysis

Initially, all data will be examined for missing, nonsensical, and outlying variables. Missing data will be treated as missing and not imputed (ie, will be analyzed on a per-protocol basis). However, an intention-to-treat analysis will be conducted to determine the clinical effects of the e-CBT program on participants who dropped out. Based on previous experience with CBT and e-CBT in similar patient populations, the anticipated dropout rate is up to 30% by the end of the treatment or TAU phases [14,33,35,37,40]. Given the likelihood of participant dropout or withdrawal, the study sample has been purposely oversampled to obtain meaningful and statistically significant results at the end of the study. Considering the effect size for e-CBT reported by Todd et al [19] for the reduction of depression symptomatology (effect size=0.44), a significance of P<.05 and a power of 0.80, a sample size of 170 (85 per arm) would be sufficient to detect significant changes from this intervention [14,19,33,35,40,41]. As this is the first study aiming to establish an e-CBT program specific for BD-II, this sample size calculation relies on data from e-CBT specific for BD (all types). It takes into account the established effectiveness of web-based psychotherapy [14].

A 2-tailed significance level of α=.05 will be used for all calculations, except when a Bonferroni correction is needed. Possible differences between program completers and noncompleters will be determined by comparing the respective demographic information using independent sample *t* tests. A 2-by-3 repeated measures ANOVA of the primary (BD symptomatology: MADRS and YMRS) and secondary (Q-LES-Q-SF and RS-14) outcomes will be conducted to compare the effects of e-CBT + TAU to TAU only throughout the 13-week treatment course (0-, 6-, and 13-week assessment points). Variables associated with outcome measures will be determined using linear regression (continuous outcomes) and binomial regression analysis (categorical outcomes). The data collected from the posttreatment survey will be analyzed qualitatively with 2 reviewers to identify common themes and specific areas for improvement. All statistical analyses will be conducted using SPSS Statistics for Mac, version 28 (IBM Corp).

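### The posttreatment survey goes only to people who completed e-CBT, so the feedback meant to improve the program omits those who stopped it

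*Protocol article*

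**What the plan says.** The Abstract (Objective) gives the tertiary aim as "gathering user feedback using a posttreatment survey to support the continuous improvement and optimization of the proposed program", and the Introduction repeats it. Outcome Evaluation names the recipients: "This posttreatment survey will be sent to all participants who completed the e-CBT program". The same section says the survey will hold "questions related to their experience going through the modules and using the OPTT platform", and will also invite further comments and suggestions. Under Data Analysis the responses are to be "analyzed qualitatively with 2 reviewers to identify common themes and specific areas for improvement".

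On attrition, Data Analysis states that "the anticipated dropout rate is up to 30% by the end of the treatment or TAU phases", and the limitations paragraph of the Discussion gives the same figure. Data Analysis also plans to compare completers with noncompleters on demographic variables, so the plan treats these as two groups. Under Procedures, control participants may take up e-CBT once their 13 weeks as controls are over. The wording of the survey rule would cover those of them who complete it.

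**The concern.** The people asked are selected on a result of the thing being evaluated. A survey meant to show what needs changing reaches only those for whom the program was workable enough to finish. People who stopped are likely to know most about modules that did not suit, platform trouble, homework load or lack of time, and the rule as written does not ask them.

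This is not ordinary nonresponse. A better response rate or a more careful thematic analysis cannot recover the views of people who were never sent the survey. At stake is whether the tertiary objective is answered for all users of the program or only for those who finished it.

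**Working it through.** **Who is asked, and who else is heard.** Each place in the article that bears on noncompleters or on program improvement was checked for whether it collects the views of those who stopped.

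- Outcome Evaluation, survey: completers only.
- Data Analysis, completers against noncompleters: demographics only. This shows who left, not why.
- Data Analysis, intention-to-treat analysis: clinical effects in those who dropped out. No feedback is collected.
- Discussion, platform user analytics: usage data, with no group named. These do not record opinions or reasons for stopping.
- e-CBT Specific for BD-II, people with lived experience: they help to develop and review the modules. They are not described as trial users who stopped.
- e-CBT Specific for BD-II, assigned therapist: asynchronous contact and homework feedback during the program. Some difficulties may surface here, but no collection of feedback from those who stop is described.

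No place in the article extends the survey to those who stop.

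**The plan's own figure.** The only calculated figure nearby is the sample size: "a sample size of 170 (85 per arm) would be sufficient to detect significant changes from this intervention", based on an effect size "for the reduction of depression symptomatology (effect size=0.44), a significance of P<.05 and a power of 0.80". A two-sided two-sample t test with these inputs needs n = 82.05, so 83 per arm and 166 in total, within 3% of the stated 170. This confirms 85 as a usable arm size. The survey point does not otherwise depend on it.

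**Number not surveyed.** Inputs: 85 allocated to e-CBT (Procedures), and a noncompletion rate d. The article gives no value for d. It gives up to 30% for dropout in either phase, which is used here as an assumed upper case. The 20% and 10% rates are assumptions chosen to show a range.

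Not surveyed = 85 × d; surveyed at most = 85 × (1 − d).

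| Assumed d | Not surveyed | Surveyed at most |
|---|---|---|
| 30% | 85 × 0.30 = 25.5 (25-26) | 85 × 0.70 = 59.5 (59-60) |
| 20% | 85 × 0.20 = 17 | 85 × 0.80 = 68 |
| 10% | 85 × 0.10 = 8.5 (8-9) | 85 × 0.90 = 76.5 (76-77) |

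Controls who later complete e-CBT would add respondents. They would again be completers, so the gap is not filled.

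**The case against.** The strongest reply is that nothing here is an error or a contradiction. The article consistently describes a posttreatment survey about going through the program, and it never sets out to learn why people stop or to measure acceptability across the whole arm. Completers can report problems too, since the survey asks for suggestions. Analytics and therapist contact give some further information. Recording reasons for withdrawal is operational detail that an article may leave to the full protocol.

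Much of this stands, and it limits the point to a cheap improvement. It does not remove it, because the sampling rule is stated in the article rather than left out, and it fits poorly with the stated purpose of finding areas for improvement.

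Four stronger readings are tempting, and the document does not support them:

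- *That 30% of e-CBT users will go unheard.* The figure is an upper bound on dropout in the treatment or the TAU phase. It is not a rate of stopping e-CBT, and completion is undefined.
- *That reported satisfaction will be inflated by a calculable amount.* With assumed rates of 90% satisfied among completers and 40% among others, the whole group would be 0.7 × 90% + 0.3 × 40% = 75%. But the analysis is qualitative and no satisfaction rate is planned, so this would be a bias in a quantity the trial does not report. A tilt toward favourable views is likely, not shown.
- *That the plan itself calls dropout its main weakness.* The Discussion gives that place to internet access and technical skill. Dropout is listed later as a further limitation.
- *That nothing will be learned about stopping.* Analytics and therapist contact give partial information.

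**Conclusion.** The point holds as a minor one. As written, the survey draws its themes only from people who completed e-CBT, and no other data collection described in the article records the views of those who stopped. Problems that led people to leave will probably be under-represented.

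The size is conditional: from about 8-9 of 85 at 10% noncompletion to about 25-26 of 85 at 30%. This assumes that noncompletion can be set equal to those rates and counts only the arm first allocated to e-CBT. Only the tertiary qualitative outcome is affected. The primary and secondary comparisons, the significance level and the power are not.

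**What to change.** Change the recipient sentence in Outcome Evaluation so that the survey goes to everyone given access to e-CBT. This includes controls who take it up later and those who stop the modules but have not withdrawn consent to be contacted. That last condition matters because the Ethics Approval section allows withdrawal at any time, and stopping the modules is not the same as leaving the study. A short version will do for those who stop, with one item on the reason. State what counts as completing the program, and report themes by completion status with the response rate in each group.

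The cost is one changed sentence, one added item on a platform that already delivers the questionnaires, and a minor notification to the ethics board. Response will probably be lower among those who stopped, which is why response rates should be shown by group.
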